### Sample size

For inappropriate admission decisions, a total sample size of 580, approximately 50 recruits per site, was calculated. Data from our group’s ongoing prospective observational study into the ability of qfFN to predict preterm birth in symptomatic women (PETRA REC Ref. 14/LO/1988) has allowed us to estimate the likely treatment effect for the intervention reducing inappropriate admissions from 25 to 10% and intra-class correlation 0.030. Based on 13 clusters this treatment effect requires approximately 580 for 80% power. We are aware that a larger number of centres would also be preferable, but believe 13 is adequate and at the limit of what is currently feasible.

For our qualitative questionnaires, we have estimated a target recruitment of 300 participants, 25 recruits per site, allowing for non-compliance and data collection errors. Based on previous research involving visual analogue scale (VAS) scores [19], a total sample size of 272 was required at standard levels of significance (alpha = 0.05 two-sided) to achieve 90% power to detect a 10% difference in mean VAS scores between hospitals with and without the intervention.

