#### **Hypothesis:** The implementation of the QUIPP app and management algorithm will decrease inappropriate management for TPTL

### Trial design

EQUIPTT is a cluster randomised controlled trial (incorporating a parallel group design) across 13 obstetric centres. This design was chosen as for this scale of protocol intervention (in an emergency situation), it would be challenging to randomise at participant level, affecting uptake and generalisability of the findings, and individual clinicians cannot be randomised to varying decision-making with individual patients.

The pragmatic approach was taken to introduce the QUIPP app to entire hospital antenatal units, as standard practice for all clinicians, and all affected pregnancies. Using this parallel cluster studies have the added value of limiting the time-bias which occurs with a stepped wedge design. Also, unlike in a crossover design, the intervention does not need to be retracted from the cluster, avoiding contamination bias. Individuals within a cluster tend to have more similar outcomes than across clusters. The similarity in the outcomes of individuals within a cluster within a time period is typically measured by the within-cluster within-period intra-cluster correlation coefficient. If this is not factored into the power calculation and analysis, the effectiveness of the intervention may be exaggerated [18].

All 13 centres will provide data related to the principal outcome under their current practice in a six-week pre-intervention data collection period. Following randomisation, the centres will use intervention (using the QUiPP app) or control (routine management) for a nine-month analysis period. In the final phase of the trial, the intervention will be introduced in the 6 control units. Following this, data will be collected for a further six weeks across all 13 sites, in order to equally incentivise all sites to participate. The QUIPP app approach will be adopted as standard practice in all sites if successful. A list of the study sites is available from the authors on request.

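### The 90% power for EQUIPTT-Q is stated without an SD, ICC or design effect for a comparison of 13 randomised hospitals, and the planned t-tests ignore clustering

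*Protocol article*

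**What the plan says.** All references are to the protocol article.

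- **Sample size, questionnaire study.** The text says "a total sample size of 272 was required", at two-sided alpha 0.05, "to achieve 90% power to detect a 10% difference in mean VAS scores between hospitals with and without the intervention". The basis is earlier VAS research, which is cited without an SD. No ICC, design effect or number of clusters is given. For recruitment, "target recruitment of 300 participants, 25 recruits per site, allowing for non-compliance and data collection errors".
- **Sample size, main trial.** The paragraph just before does give clustering inputs: an effect "reducing inappropriate admissions from 25 to 10% and intra-class correlation 0.030", and 13 clusters.
- **Randomisation.** Centres were randomised, seven to one group and six to the other.
- **Trial design.** On within-cluster correlation: "If this is not factored into the power calculation and analysis, the effectiveness of the intervention may be exaggerated".
- **Data analysis, Women's experience study.** VAS anxiety and DCS scores are to be compared between hospitals with and without the app by t-tests (independent samples, and paired where appropriate), or by non-parametric equivalents if the data are not normal. The random effect for clustering is described only under the Cluster randomised trial heading.
- **Outcomes, Women's experience study.** The key outcome is the before-to-after difference in VAS anxiety, compared between hospitals with and without the app.

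**The concern.** The questionnaire comparison has the same randomised units as the main trial: 13 hospitals. Women assessed in one hospital share staff, setting and practice, so their scores may be correlated and carry less information than the same number of independent women. The protocol states this principle, applies it to the admission outcome, and then shows no sign of it in the next paragraph or in the EQUIPTT-Q analysis.

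Two things are at stake. If clustering was left out of the 272, a null anxiety result would be read as coming from a 90%-powered study when its power was lower. And if plain t-tests are used on clustered data, a positive result would be declared too easily. The second problem exists however 272 was obtained.

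**Working it through.** **Inputs from the article:** two-sided alpha 0.05; power 90%; N = 272; target 300; 13 sites split 7 and 6; ICC 0.030 (for inappropriate admissions only).

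**Assumptions:** a 10% difference means 10 points on a 0–100 scale; the VAS SD and ICC are not given, so the SD is back-solved and the ICC is varied from 0.01 to 0.05.

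**1. Can 272 be reproduced?** Not uniquely, because the SD is missing. With n per arm = 2(1.960 + 1.282)² / d², two readings fit.

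- *Reading A, no design effect.* n = 136 per arm gives d = 0.393 (0.394 with a 7:6 split or a t-test calculation). For 10 points the SD is 10/0.394 = 25.4. A round SD of 25 gives 132 per arm, 264 in total.
- *Reading B, design effect included.* SD 20 gives d = 0.5 and 85 per arm, 170 in total. With 21 per site and ICC 0.03, the design effect is 1 + 20 × 0.03 = 1.60, and 170 × 1.60 = 272.

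**2. Power with 13 sites.** For a test that holds its 5% level:

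- m = N/13 and DE = 1 + (m − 1) × ICC
- SE of the difference, in SD units = √[(DE/m)(1/6 + 1/7)]
- noncentrality = d/SE
- normal approximation: power = Φ(d/SE − 1.96)
- small-sample version: noncentral t on 13 − 2 = 11 degrees of freedom (critical value 2.201)

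Example, reading A, N = 272, ICC 0.03: m = 20.92; DE = 1.598; SE = √(0.07638 × 0.3095) = 0.1538; d/SE = 0.394/0.1538 = 2.56; power = Φ(0.60) = 73%, or 65% on 11 df.

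| Reading A (d = 0.394) | ICC 0.01 | ICC 0.03 | ICC 0.05 |
|---|---|---|---|
| 272 analysed, normal / 11 df | 84% / 77% | 73% / 65% | 63% / 55% |
| 300 analysed, normal / 11 df | 87% / 80% | 75% / 67% | 65% / 57% |

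Reading B (d = 0.5, ICC 0.03):

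- N = 272: d/SE = 0.5/0.1538 = 3.25, which gives 90% by normal approximation and 84% on 11 df.
- N = 300: m = 23.08, DE = 1.662, SE = 0.1493, d/SE = 3.35, which gives 86% on 11 df.

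**3. Type I error of an unadjusted t-test.** With m = 20.92, the approximate true level is 2[1 − Φ(1.96/√DE)]:

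- ICC 0.01: DE 1.199, about 7%
- ICC 0.03: DE 1.598, about 12%
- ICC 0.05: DE 1.996, about 17%

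**4. Per-site figure.** 25 × 13 = 325, whereas 300/25 = 12 sites and 300/13 = 23.1 per site. The allowance for incomplete data is 272/300 = 91%.

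**The case against.** A reader might infer that the calculation contains no design effect and that the study's power is therefore two-thirds to three-quarters. The document does not establish this. Back-solving an SD of about 25 presupposes that clustering was left out, so it cannot also prove it. SD 20 with the trial's own ICC gives the same 272. A condensed article may also leave the SD and ICC of a secondary study to the full protocol or to the cited work. This part of the objection stands: the lower power figures are conditional.

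The ICC of 0.03 belongs to an admission decision, and self-rated anxiety may cluster less. At ICC 0.01 with 300 women analysed, power is 87% (80% on 11 df) even under reading A. That also stands, and is why a range is needed. So does the point that the key outcome is a before-to-after change, whose SD and ICC may differ from those of a single VAS score.

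A third possibility is that 272 came from a calculation that already used 11 degrees of freedom. At ICC 0.03 that requires an effect of about 0.548 SD, an SD of 10/0.548 = 18.2. Nothing in the article suggests this, but only the missing inputs can rule it out.

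The objection does not reach two points. The t-tests are a stated method, not an omission, and they conflict with the Trial design section. The per-site count does not multiply out to the total.

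**Conclusion.** The point holds in a conditional form. The 90% is unsupported as written: no SD, ICC or design effect stands behind it, and the named analysis ignores the clustering that the protocol says must be accounted for.

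The t-test plan makes an individual-level calculation the more natural reading, but does not settle it. On that reading, power at 272 is about 73% (65% on 11 df) at ICC 0.03, with a range of 84% / 77% to 63% / 55% over ICC 0.01 to 0.05. On the favourable SD 20 reading, 90% holds only by a normal approximation that takes no account of there being just 13 clusters; on 11 df it is about 84%, or 86% with 300 analysed. These figures rest on the assumed SD and ICC and on reading 10% as 10 points.

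The inflated type I error of the plain t-tests does not depend on how 272 was derived, only on the ICC. The 325 versus 300 discrepancy needs no assumption.

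This should be fixed, but it concerns a secondary study; the main trial's outcome and sample size are not affected.

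**What to change.** 1. State the SD and ICC behind 272, say whether 10% means 10 points, and say whether the figures refer to a single VAS score or to the before-to-after change named as the key outcome.
2. Replace the unqualified 90% with the power, or the detectable difference, for 13 clusters on 11 degrees of freedom, over a range of ICCs. Figures such as 67% to 75% (300 women, ICC 0.03) should be printed only if the stated inputs confirm that 272 was an individual-level number.
3. For between-hospital comparisons of VAS and DCS, replace the independent-samples t-tests and their non-parametric equivalents with a cluster-adjusted method with a small-sample correction, such as a cluster-level analysis on 11 degrees of freedom.
4. Correct 25 per site to about 23 (300/13), or the total to 325.

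The cost is a few restated figures and a changed analysis sentence. No extra recruitment or data collection is needed.

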### Randomisation

Randomisation is at the cluster level. Centres have been randomly allocated to receive either intervention or control. Due to there being an odd number of centres, seven sites were allocated to one group and six to the other. Minimisation of the randomisation list was not appropriate for this design but the imbalances between three levels of NICU facility at intervention and control sites were small (4:3, 3:2, and 0:1). TPTL rates were known for 10 sites and the difference between the average rates at control and interventions sites were within chance (72 and 89%).

### Data analysis

#### Cluster randomised trial

Data analysis will follow the intention to treat principle, according to the planned intervention. Data will be analysed using Stata software Version 14 or later (StataCorp, College Station, Texas) to estimate the size and test for statistical significance of any effects of the intervention on primary and secondary, and analysis will be supervised by the trial statistician, [name]. A per protocol analysis will also be performed, excluding those who are incidentally admitted or treated for reasons unrelated to preterm labour. Treatment effects for binary endpoints will be expressed as risk ratios (relative risk) with 95% CIs, using binomial regression and adjusting for variables used in the minimization process. Risk differences will also be calculated for the primary endpoint. The analysis model will include a random effect for clustering and adjusted standard errors for clustering. Adjustments will also need to be made for differences between cluster populations, such as ethnicity and maternal age. Our primary outcome of inappropriate decisions will be measured per 1000 deliveries.

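### The primary model adjusts for minimisation variables although no minimisation was done, which leaves only an open covariate list

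*Protocol article*

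**What the plan says.** The analysis section of the protocol article (Data analysis, Cluster randomised trial) gives risk ratios for binary endpoints from binomial regression, "adjusting for variables used in the minimization process". On clustering it adds: "The analysis model will include a random effect for clustering and adjusted standard errors for clustering". It then says: "Adjustments will also need to be made for differences between cluster populations, such as ethnicity and maternal age".

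The Randomisation section says: "Minimisation of the randomisation list was not appropriate for this design". It describes the centres only as randomly allocated, seven to one group and six to the other. It reports NICU level and the rate of threatened preterm labour as balance checks on the finished allocation.

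The Trial design section says: "All 13 centres will provide data related to the principal outcome under their current practice in a six-week pre-intervention data collection period". The analysis section does not mention these data.

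**The concern.** The first part of the stated covariate set does not exist. An analyst who follows the text has no minimisation variable to enter, and so no named site-level covariate. The second part is not closed. It gives two examples and ties adjustment to differences between clusters, which reads as permission to choose covariates once those differences are known.

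With 13 clusters, the choice of covariates can move the estimate and its standard error. If the list is settled late, the primary result is open to challenge however it turns out. A measure of each site's habits before the intervention is planned everywhere, yet the article does not say whether the model uses it.

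**Working it through.** **The two sections side by side.** The analysis section presupposes minimisation, and the Randomisation section rules it out. No minimisation variable is named anywhere in the article. Two variables could be guessed from the Randomisation section, and neither repairs the phrase:

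- The rate of threatened preterm labour was known for 10 sites, so adjusting for it would lose three clusters or need imputation.
- NICU level has three levels, split 4:3, 3:2 and 0:1. The columns sum to 7 and 6, so with 6 control units the lone site is a control. In a three-level factor that site has no comparator in its own level and adds nothing to the treatment contrast.

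**The plan's own figure first.** Inputs from the Sample size section are 580 women, 13 clusters, 25% v 10% and ICC 0.030. There are 6 control and 7 intervention sites. Two-sided 0.05 is assumed, because the article states it only for the questionnaire study. The calculation is a cluster-level comparison of proportions, used as an approximation to the binomial model.

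- Women per site: m = 580/13 = 44.6.
- Design effect: 1 + (44.6 − 1) × 0.03 = 2.308.
- Variance of a site proportion: control 0.25 × 0.75 × 2.308/44.6 = 0.00970; intervention 0.10 × 0.90 × 2.308/44.6 = 0.00466.
- Variance of the difference: 0.00970/6 + 0.00466/7 = 0.00228; SE 0.0478.
- Noncentrality: 0.15/0.0478 = 3.14. With 13 − 2 = 11 df, power is **81.5%**, against the stated 80%.

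The stated sample size is therefore adequate without covariates and does not depend on this point.

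**If NICU level were entered as three levels and explained no variance.** Degrees of freedom fall to 9. Counting only that loss, power is 79.8%. Removing the lone control site from the contrast as well (0.00970/5 + 0.00466/7 = 0.00261; noncentrality 2.94) gives about 74.4%.

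**What the baseline proportion could add.** Assume uniform accrual, so that six weeks out of 39 yields m₀ = 44.6 × 6/39 = 6.9 women per site. The reliability of a site proportion is R = m × ICC/[1 + (m − 1) × ICC].

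- Baseline: R₀ = 0.175. Trial period: R₁ = 0.580.
- With cluster autocorrelation c, the squared correlation is r² = c² × R₀ × R₁ = c² × 0.102. The variance is multiplied by 1 − r², with 10 df.

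| c (assumed) | Variance factor | Power |
|---|---|---|
| 1.0 (stable site effects) | 0.90 | 84.7% |
| 0.8 | 0.94 | 83.2% |
| 0.6 | 0.96 | 82.1% |

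The gain over 81.5% is about 0.6 to 3 points after paying for one df. These figures take the baseline means of the two arms as equal. Estimating the slope from 13 sites costs on average a further factor of 1 + 1/(13 − 4) = 1.11 in variance, and 0.90 × 1.11 is about 1.0. The table is therefore a best case.

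**The case against.** The best defence is that this is a condensed article. A full covariate list and the role of baseline data normally sit in the analysis plan, which is not shown. That argument stands for the baseline data. A reader might infer that the six-week outcome will go unused, but the analysis section is silent on it and its open list does not exclude it. The silence alone is no finding.

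A reader might also infer that the primary estimate is biased or that the trial is underpowered. Neither follows. A randomised comparison without site-level covariates is unbiased, clustering is in both the model and the sample size, and power is 81.5% unadjusted.

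Nor do the documents support a claim of marked imbalance. The article calls the NICU differences small and the difference in rates of threatened preterm labour (72 and 89%) within chance. With 7 and 6 sites, 4:3 and 3:2 are close to as even as they can be. The plan does not propose a three-level NICU factor, so that calculation only shows why the phrase cannot be repaired by guesswork.

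The argument does not rescue the minimisation phrase. The article states that adjustment and contradicts it in its own Randomisation section, so it is not a detail left for later.

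**Conclusion.** The contradiction is real and lies in the primary model. As written, the adjustment set is empty apart from an open list that could be filled once cluster differences are known. This part rests on the text alone and needs no assumption.

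Using the baseline outcome is an improvement to recommend, not an error to correct. At the article's ICC of 0.03 the gain is up to about 10% in variance, or roughly 0.6 to 3 power points. This rests on uniform accrual (about 7 baseline women per site) and an assumed cluster autocorrelation of 0.6 to 1.0, neither of which the article gives. Larger gains would need a larger ICC than the article states. The case for acting is that the primary model should be fixed in advance; extra power is secondary.

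**What to change.** - Delete the reference to minimisation variables.
- Replace the open wording with a short, closed covariate list, fixed before unmasking. Name the individual-level covariates, for example maternal age and ethnicity.
- Include each site's pre-intervention proportion of inappropriate decisions in that list, and state its role explicitly.
- If NICU level was what the phrase meant, say so and do not enter it as three levels.
- Report the unadjusted estimate alongside.

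The cost is a change of wording and one cluster-level degree of freedom for the baseline term. If that term explained nothing, losing the degree of freedom would take power from 81.5% to 80.7%. The data are already due to be collected.

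### The primary analysis relies on many-cluster methods for 13 hospitals and states no small-sample allowance; with normal-reference inference, 5% tests would reject about 8-12%

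*Protocol article*

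**What the plan says.** The Data analysis section of the protocol article (Cluster randomised trial) commits to an effect measure and a model: "Treatment effects for binary endpoints will be expressed as risk ratios (relative risk) with 95% CIs, using binomial regression". On clustering it adds: "The analysis model will include a random effect for clustering and adjusted standard errors for clustering". Stata is the named software. The section also plans adjustment for differences between cluster populations. It names no reference distribution, degrees of freedom or small-sample variance correction.

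The number of clusters is fixed. Under Randomisation, "seven sites were allocated to one group and six to the other", and Trial design identifies the smaller group: "the intervention will be introduced in the 6 control units". So there are 7 intervention and 6 control hospitals.

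The Sample size section assumes "reducing inappropriate admissions from 25 to 10% and intra-class correlation 0.030" and concludes: "Based on 13 clusters this treatment effect requires approximately 580 for 80% power". It concedes that more centres would be preferable but considers 13 adequate.

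**The concern.** A maximum-likelihood random effect and a cluster-robust standard error both estimate between-hospital variation from the hospitals themselves. Read against a normal distribution, both assume that this variation is well estimated. With 6 hospitals in one arm and 7 in the other it is not: the standard error tends to be too small, and 1.96 ignores how uncertain it is. Using both devices together does not remove the problem.

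The stake is the primary claim. A false-positive rate near twice nominal, with intervals that under-cover, would weaken a result meant to inform national guidelines. The Trial design section itself warns that neglecting within-cluster correlation in power and analysis can exaggerate effectiveness.

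**Working it through.** **Inputs from the article.** 13 clusters, 6 control and 7 intervention; N = 580; 25% v 10%; ICC 0.030; 80% power.

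**Assumptions.** Two-sided alpha 0.05 for the primary outcome (the article states it only for the questionnaire study; the 95% CIs agree with it). Beta-binomial clustering. Site-size CV from 0 to 0.65, since none is given. Unequal sizes are likely, because sites enrol consecutive women. No covariates in the simulations.

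**1. The plan's own figure.**
- Mean cluster size m = 580/13 = 44.6.
- Design effect = 1 + (44.6 − 1) × 0.030 = 2.31.
- Variance of the risk difference = (2.31/44.6) × (0.25×0.75/6 + 0.10×0.90/7) = 0.00228, so SE = 0.0478.
- Effect/SE = 0.15/0.0478 = 3.14.
- Power, normal reference: Φ(3.14 − 1.96) = 88%.
- Power, noncentral t: 81.5% on 11 df (13 − 2), 80.7% on 10, 79.8% on 9.

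With equal sites, the t calculation comes close to the stated 80%. With unequal sites the design effect is 1 + ((1 + CV²)m − 1) × ICC. At CV 0.65 this is 2.87, effect/SE is 2.81, and normal-reference power is 80.3%. So 580 is compatible with either reference.

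**2. The critical value alone.** If a statistic truly follows t on 11 df, comparing it with 1.96 rejects 7.6% under no effect. Interval length ratio: 1.960/2.201 = 0.89, so 11% too short, before any downward bias in the standard error.

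**3. Simulated type I error at nominal 5%.** 6 v 7 clusters, about 580 women, event rates 25% and 10%. The sandwich and cluster-level rows use 60,000 runs per setting; the random-intercept rows use about 8,000.

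| Analysis | Normal reference | t on 11 df |
|---|---|---|
| Sandwich log risk ratio with 13/12 factor, equal sites, ICC 0.01-0.05 | 8.6-9.6% | 5.8-6.6% |
| Same, ICC 0.03, CV 0.4 | 9.9-10.3% | 6.9-7.2% |
| Same, ICC 0.03, CV 0.65 | 11.4-11.9% | 8.1-8.4% |
| Random-intercept logistic, model-based SE | 9.1-9.6% | 5.9-6.3% |
| Random-intercept logistic, robust SE | 8.4-9.4% | 5.9-6.2% |
| Test on 13 site proportions | 7.3-7.8% | 4.7-5.1% |

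Without the 13/12 factor the sandwich reaches 13.2% at CV 0.65. A linear random-intercept analogue gave 7.3-9.7% by maximum likelihood and 6.1-7.5% by restricted maximum likelihood, so a few variants fall below 8%.

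Moving only the critical value to t on 11 df leaves the ordinary sandwich at about 6-8%. The cluster-level t-test holds its level.

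**4. Power at 580 with t-based inference.**

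| Site-size CV | Design effect | Effect/SE | 11 df | 9 df |
|---|---|---|---|---|
| 0 | 2.31 | 3.14 | 81.5% | 79.8% |
| 0.5 (assumed) | 2.64 | 2.93 | 76.2% | 74.3% |

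Nine df corresponds to two site-level parameters, for example a three-level NICU factor.

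**The case against.** The strongest reply is that the article is silent rather than wrong. It does not say that a normal reference will be used or that a correction will be omitted, and nothing in its wording excludes t critical values or a bias-corrected sandwich, which is itself a cluster-adjusted standard error. Such detail commonly sits in the analysis plan. This stands to the extent that the 8-12% must be conditional. A reader might infer that the primary test will run at about twice its nominal level; the document does not fix that. What remains is that the article commits to a class of method whose usual inference is poor at 7 v 6, and that a better one is available at little cost.

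A reader might also infer from 580 that the sizing assumed t-based inference which the analysis then drops. The arithmetic does not support this: on 11 df, 80% power needs only 530, and a normal reference with CV 0.65 gives 80.3% at 580. Nor does the sizing prove that few clusters were allowed for.

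Two further limits are fair. The simulations are unadjusted, and the random-effect version is logistic rather than the adjusted binomial risk-ratio model, so they approximate the stated analysis. And nothing shows that pairing a random effect with robust standard errors is worse than either alone: 8.4-9.4% against 9.1-9.6%. The pairing does not cure the problem; it is not shown to add to it.

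**Conclusion.** The point holds in conditional form. The article specifies a random effect with cluster-adjusted standard errors for 13 clusters and states no small-sample allowance. Under normal-reference inference the type I error would be about 8-12% rather than 5%, and 95% intervals would be at least 11% shorter than those using t on 11 df with the same standard error as a starting point. The range rests on beta-binomial clustering, ICC 0.01-0.05, an assumed site-size CV of 0-0.65 and an assumed two-sided 5% level. The planned size is not shown to be wrong. The analysis plan is not shown and may already resolve this.

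**What to change.** Before any comparison by arm, name one few-cluster method and use it for primary and secondary outcomes. Either:

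- a cluster-level analysis of site proportions, covariate-adjusted in two stages, with t on 11 df less the number of site-level covariates; or
- a GEE or modified Poisson model with a bias-corrected sandwich (Kauermann-Carroll or Mancl-DeRouen) and the same df.

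Choose the variance correction and the df together, since t on 11 df with an ordinary sandwich is not enough when sites differ in size. Keep site-level covariates few, because each uses part of the 11 df.

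The cost is analysis wording and wider intervals: a factor of 1.12 on 11 df (2.201/1.960), or 1.15 on 9 df. Any statement that 580 still gives about 80% power should carry the qualification that this needs roughly equal site sizes; the site-size CV should be given with it. If the analysis plan already names such a method, one sentence confirming it closes the point.
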